**Fig. 2 Fig2:**
[figure not shown]
Process for collecting post-discharge follow-up data

#### Patient-level routine data

In addition to the self-report data outlined above, routine data will be extracted from the consented patients’ medical records. Data includes:
Recorded discharge date for the index admission—to ensure accurate discharge dates are recorded during the trial;Emergency hospital readmission dates up to 90-days post-discharge—to assess the feasibility of collecting our primary outcome measure in the definitive cRCT, and to calculate the length of stay for any readmissions;Ward moves that occurred prior to discharge during index admission—to assess intervention fidelity and contamination between wards.

Due to funding and progression of the PACT programme of work, the research team face tight timescales between finishing the feasibility trial and starting the definitive trial. As this study does not assess effectiveness, if the Trial Management Group decide that we already have enough data to assess the feasibility of progressing to a definitive trial, we may decide not to collect questionnaire and routine readmission data up to the full 90-days post-discharge for patients who are recruited later in the study.

#### Ward-level routine data

To explore what ward level baseline data are required for the definitive cRCT, the following non-identifiable data will be extracted for each participating ward over the most recent 12-month period:
The total number of patients discharged from a participating ward and the total number of these patients who are readmitted to the hospital Trust (any ward) within a 30-day period (split by patients who are < 75 years and ≥ 75 years);Average length of stay for patients admitted to each participating ward (split by patients who are < 75 years and ≥ 75 years with monthly totals);

In addition, the total number of admissions to participating wards during the recruitment period (split by < 75 years and ≥ 75 years) will be used to identify how many patients aged 75 years and over were admitted to the ward but not screened.

### Statistical analysis

A full statistical analysis plan will be drafted before the completion of data collection. Quantitative analysis will focus on descriptive summaries for each treatment group including the number of wards and patients approached, randomly assigned, receiving intended treatment, and providing outcome data. A CONSORT diagram for cluster trials will document the flow of participants through the study. The percentage of participants readmitted will be determined. The degree of clustering using intracluster correlation coefficients (with 95% confidence intervals) may also be quantified, acknowledging that this may be unreliable due to the small sample size [30].

Participant withdrawals, reasons for withdrawal, and non-responses at each data collection point will be summarised and compared by trial arm. Recruitment and attrition rates (ward and patient) across the two arms will be compared, along with outcomes data at follow-up. All baseline and outcome data will be summarised descriptively by trial arm using means and standard deviations for continuous variables and counts and percentages for categorical data. Participants will be summarised by their randomised ward irrespective of whether they received the actual allocation or not. PACT-M data will also be analysed to define cut-offs for a high versus low-quality transition. There are no planned interim analyses.

Qualitative and quantitative data will be used to assess the following criteria when deciding whether to progress to a definitive cRCT:
2–8 eligible wards exist within participating trusts (depending on size) and narrative indications of staff interestAverage of 4 patients per ward per month recruitedAttrition less than 10% for the primary outcomeStaff, patients, and carers positively evaluate the intervention (or modifications can be made to address any concerns).

Fulfilment of these progression criteria will be discussed and agreed with our Trial and Programme Management Groups, our independent Trial Steering Committee, and the funders (the National Institute for Health Research).

### Embedded qualitative assessment of feasibility

Qualitative methods will be embedded within the feasibility study to explore the acceptability, usefulness, and feasibility of the intervention, and explore how fidelity can be assessed.

#### Sample

On intervention wards, purposive and opportunity sampling will be used to recruit a nested sample of 20–24 patients (3–4 patients per ward). Patients will consent to patient-level observations and interviews in addition to the quantitative post-discharge follow-ups. Carers (e.g. spouse or child) who are involved in a patient’s care will also be recruited to participate. Patients will receive up to £30 as a thank you for their participation.

Multidisciplinary staff involved in the facilitation meetings and implementing the intervention will be purposively sampled to participate in interviews and/or ward-level observations. In addition, one staff member on each control ward will be recruited at the end of the study to participate in an interview (*n* ≤ 28).

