### Study design

A cluster randomised controlled feasibility trial will be conducted on ten wards (the clusters) within three acute NHS Trusts in the Yorkshire and Humber region of the UK. Cluster designs are used when there is a significant risk of contamination occurring if individual patients within a ward were randomised. Since this study includes a ward level component, it was not possible to use individual randomisation. Wards will be randomised to deliver either the YCNY intervention or usual care.

A minimum of 200 patients (20 per ward) will be recruited across intervention and control wards to complete questionnaires at baseline and then three time-points following discharge from hospital—5- to 14-, 30-, and 90-days post-discharge. Routine data regarding the patients’ index hospital admission and any subsequent readmissions (up to 90-days post-discharge) will be extracted from their medical record.

An embedded qualitative evaluation will assess the feasibility and acceptability of the intervention and implementation package. Up to 24 patients and their carers will be recruited from intervention wards to participate in patient-level observations of care and individual interviews. Up to 28 staff will be recruited to participate in interviews and ward-level observations.

In addition, a sub-study will be conducted alongside the feasibility trial to explore the most efficient, cost-effective, and accurate way of gathering primary outcome data (30-day emergency hospital readmissions) within the definitive cRCT. Approval has been sought from the Confidentiality Advisory Group (CAG) to access the medical records of 100 patients (10 per ward) without consent to understand the actual destinations of patients who are discharged to their ‘usual place of residence’.

Figure 1 details the schedule of study enrolment, interventions, and assessments. The SPIRIT checklist [18], which details the recommended items to include in a clinical trial protocol, is available in Additional file 1.

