##### YCNY booklet

This patient-facing booklet is given to patients at the start of admission to a participating ward and is designed to be used throughout their stay and following discharge. Focusing on the four key functions, the booklet provides information as to why patients should ‘know more’ and ‘do more’ in hospital and gives suggestions as to how they could do this. The booklet contains ‘I would like to talk about’ pages which patients can use to indicate to staff that there is something they would like to discuss. There are spaces for patients, carers, or staff to make notes.

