#### Patient post-discharge follow-up questionnaires

Following discharge from hospital, patients will be sent postal questionnaires at three time points—5-, 30-, and 90-days post-discharge. These time points represent a critical safety period (immediately post-discharge), are policy-relevant (30-days), and allow assessment of longer-term effects (90-days). To try and increase response rates, patients will receive a £5 voucher with the questionnaire at each time point [29]. Measures include the Partners At Care Transitions Measure (PACT-M) [26], Care Transitions Measure (3 items—CTM-3) [27], EuroQol 5-Dimension Health Questionnaire (5 levels) (EQ5D-5 L) and Proxy EQ5D-5 L [24], and the adapted Client Service Receipt Inventory (CSRI) [28] (see Table 1 for further details). Questions will also be asked to assess receipt and thereafter, the usefulness of the intervention.

Figure 2 outlines the process for collecting post-discharge follow-up data. Patients will choose to be followed up by post alone or to additionally receive telephone support. Those choosing the latter will be telephoned approximately 3 days after the first postal questionnaire is sent. If questionnaires are not returned, a postal reminder will be sent 10 days later and a final attempt to collect data will be made via telephone to all patients regardless of follow-up choice. We will attempt to collect data at each time point unless patients explicitly withdraw from the study. The mortality status of patients will be checked prior to each follow-up time point.

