##### Observations

Patient- and ward-level observations will explore how patients, carers, and staff interact with the intervention during the patient stay and at discharge. Patient-level observations will include the introduction of the booklet, occasions where staff and patients interact as part of routine care (e.g. ward and medicine rounds), and at discharge. Ward-level observations are likely to include the facilitation session and support required to embed the intervention, staff training, staff roles in using the booklet, and ward level activities (e.g. daily cares, ward rounds, medication rounds, meetings, briefings, and handovers). Observations will be captured through field notes and ‘contact summary forms’ will be completed for each ‘contact’ (e.g. a discrete piece of observation, or something less bounded such as a day spent observing ward activity).

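### Nested qualitative patients come only from intervention wards and also supply the main questionnaire data, so by-arm response and patient-reported figures can be shifted, in either direction, by research contact that controls do not get

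*Protocol article*

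**What the plan says.** All references are to the protocol article.

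- **Where the nested patients come from.** Study design: "Up to 24 patients and their carers will be recruited from intervention wards to participate in patient-level observations of care and individual interviews". The Sample subsection gives the number as 20–24, at 3–4 per intervention ward, chosen by purposive and opportunity sampling. For control wards it describes one staff interview each and no patient-level work.
- **They also supply main-trial data.** Sample: "Patients will consent to patient-level observations and interviews in addition to the quantitative post-discharge follow-ups".
- **Payment.** Sample: "Patients will receive up to £30 as a thank you for their participation". In both arms, under the follow-up questionnaires section, "patients will receive a £5 voucher with the questionnaire at each time point".
- **Contact.** Observations: "Patient-level observations will include the introduction of the booklet", and also routine care and discharge. Interviews: one of 30–60 minutes just after discharge, and a second at 30 days if the patient still uses the intervention.
- **Analysis.** Statistical analysis: "Recruitment and attrition rates (ward and patient) across the two arms will be compared, along with outcomes data at follow-up". The same section compares withdrawals and non-response by arm at each data collection point and summarises participants by randomised ward. It gives the nested patients no separate treatment.

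**The concern.** Retention is listed under Outcomes as a main feasibility measure, and one study aim is to find the best way to follow up this population. Questionnaire response by arm is therefore something the study is meant to deliver.

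In one arm, that figure mixes patients followed up in the ordinary way with a sizeable group who were also observed, interviewed and paid for taking part in the qualitative work. The interviews fall near the 5-day and 30-day questionnaires and cover usefulness, which the questionnaires also ask about. The group is also not randomly chosen, so it may differ from other patients on the same wards before any extra contact takes place.

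A difference between arms in response, withdrawal, PACT-M, CTM-3 or EQ5D-5L could then partly reflect this one-sided contact. The intervention-arm figure for self-reported receipt is open to the same influence. These figures would inform planning of the definitive trial, which is to gather its primary outcome from 7000 patients, few of whom could be expected to have such contact.

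**Working it through.** **Inputs from the article.** There are 10 wards with 20 patients each (Study design; Patient population and sample size). Six wards are intervention and four control (Randomisation). The nested sample is 20–24 (Sample). The article gives no expected questionnaire response or receipt rate, so those below are assumptions shown over a range.

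**Reproducing the plan's figures.** 10 × 20 = 200, as stated. The arms are 6 × 20 = 120 and 4 × 20 = 80. Six wards at 3–4 each give 18–24 nested patients against the stated 20–24. The upper end matches and the lower end is two short, which does not matter here.

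**Share of the arm.** 20/120 = 16.7% and 24/120 = 20.0%, against 0/80 in controls. If wards recruited only at the progression rate of four per month for four months, the intervention arm would be 4 × 4 × 6 = 96 and the share 20.8–25.0%.

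**Questionnaire response.** Shift in the arm = share × (response in nested patients − response in other intervention patients). The largest upward shift has all nested patients responding: share × (1 − r), where r is response in the others. For scale, the standard error of the arm difference, ignoring clustering, is √[r(1 − r)(1/120 + 1/80)].

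| r (assumed) | Rise, share 16.7% | Rise, share 20.0% | SE of arm difference |
|---|---|---|---|
| 60% | 6.7 points | 8.0 points | 7.1 points |
| 70% | 5.0 points | 6.0 points | 6.6 points |
| 80% | 3.3 points | 4.0 points | 5.8 points |
| 90% | 1.7 points | 2.0 points | 4.3 points |

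The formula works equally in the other direction. If interview burden made nested patients respond 10 points less often, the arm would fall by 0.167 × 10 = 1.7 to 0.20 × 10 = 2.0 points.

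**Patient-reported outcomes.** A shift of 0.2–0.5 SD in nested patients moves the arm difference by 0.167 × 0.2 = 0.03 SD to 0.20 × 0.5 = 0.10 SD. The standard error is √(1/120 + 1/80) = 0.14 SD.

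**Self-reported receipt (intervention arm only).** If all nested patients report receipt and 40%, 60% or 80% of the others do, the arm figure becomes 50–52%, 67–68% or 83–84%.

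**After setting the nested patients aside.** 120 − 24 = 96 to 120 − 20 = 100 intervention patients remain against 80 controls. At r = 70% the standard error goes from 6.6 points to √[0.21 × (1/100 + 1/80)] = 6.9 points. With 96 remaining it is also 6.9.

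**The case against.** Several points can fairly be made on the other side.

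- **Only intervention patients can judge the intervention.** This stands. Drawing the interview sample from intervention wards suits an acceptability aim, and nothing here asks for control interviews.
- **The study is descriptive and does not test effectiveness.** This stands too: no hypothesis test is invalidated. The by-arm comparisons are nevertheless planned, and retention is a main outcome.
- **The separate tabulation may be in the analysis plan.** It may, and its absence from the article is not the fault. The point is the one-sided contact combined with the planned arm comparisons. That the nested patients are pooled is a strong inference from the wording of the Sample and Statistical analysis sections, not an explicit statement.
- **Follow-up procedures are otherwise the same in both arms.** The vouchers, the choice of telephone support and the final telephone attempt apply to everyone, which narrows the contrast. Nothing ties the £30 to returning a questionnaire.

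A reader might go further and infer three things that the article does not support.

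1. *The intervention arm will look too good.* The direction is not known. A 30–60 minute interview soon after discharge, in people who may still be unwell, could lower response as easily as contact and payment could raise it.
2. *The progression criterion of less than 10% attrition is compromised.* It concerns the primary outcome. Under Patient-level routine data, readmissions come from medical records, so interviews and payment should hardly affect it, except through withdrawals.
3. *Delivery to observed patients is not routine, so fidelity rates will be inflated.* The booklet section says "This patient-facing booklet is given to patients at the start of admission to a participating ward", but the article does not say when nested patients consent relative to that, and an early approach is not ruled out. Ward staff introduce the booklet while researchers observe. The observations are recorded as field notes for qualitative analysis, and no fidelity rates from them are planned. An observer effect is possible but not established.

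**Conclusion.** The point holds as a modest one. Between 17% and 20% of the intervention arm, and none of the control arm, has research contact and payment beyond ordinary follow-up while also supplying the main questionnaire data. The share assumes 20 patients on each of six wards and a nested sample within those 120.

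The by-arm comparisons of questionnaire non-response, withdrawal and patient-reported outcomes can be shifted as a result, in a direction the documents do not settle. Self-reported receipt is affected as an intervention-arm figure and not as an arm contrast, because control wards deliver usual care.

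Under the assumed response rates the upward limit is 1.7–8.0 points. It exceeds one standard error only in the most extreme case (60% response in the others, 20% share). The assumed patient-reported shifts stay below one standard error. The standard errors ignore clustering.

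The reason to act is that this is a systematic difference between arms that can be made visible at almost no cost, not that it is large.

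**What to change.** 1. Add a variable to the dataset that flags every patient in the observation and interview sample.
2. Keep the all-participant summary by randomised ward as the main presentation. A table without the nested patients should not replace it, because that would drop a purposively chosen group from one arm only.
3. Add to the Statistical analysis section a sensitivity table without the nested patients. It should cover questionnaire response at each time point, withdrawal, self-reported receipt and usefulness, PACT-M, CTM-3 and EQ5D-5L, with 96–100 intervention patients against 80 controls.
4. Read the two sets of figures side by side when planning retention and receipt for the definitive trial.

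The cost is one variable and one extra set of descriptive tables. Those tables are slightly less precise and leave out a non-randomly chosen group, so a difference from the main tables could reflect who was selected as well as the extra contact. They should be labelled accordingly.

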#### Data collection methods

##### Interviews

Semi-structured interviews will be conducted with patients, carers, and staff to explore acceptability, usability, usefulness, and feasibility of the intervention components (both fixed and flexible) and to explore how implementation worked within the ward context. Suggestions about optimising the intervention and implementation package will be gathered. Patient interviews lasting 30–60 min will take place just after discharge and will be conducted either at the patient’s home or over the telephone. If patients continue to use the intervention at home, a second interview will be conducted at 30-days post-discharge. Staff interviews will last 15–30 min. Interviews with staff on control wards will explore any activities that are similar to those that would meet the functional aims of the intervention (e.g. End PJ Paralysis Initiatives) and thus appear to ‘dilute’ the effect of the intervention, or serve as evidence of contamination. Interviews will be audio-recorded where possible, otherwise, detailed field notes will be taken.

##### Observations

Patient- and ward-level observations will explore how patients, carers, and staff interact with the intervention during the patient stay and at discharge. Patient-level observations will include the introduction of the booklet, occasions where staff and patients interact as part of routine care (e.g. ward and medicine rounds), and at discharge. Ward-level observations are likely to include the facilitation session and support required to embed the intervention, staff training, staff roles in using the booklet, and ward level activities (e.g. daily cares, ward rounds, medication rounds, meetings, briefings, and handovers). Observations will be captured through field notes and ‘contact summary forms’ will be completed for each ‘contact’ (e.g. a discrete piece of observation, or something less bounded such as a day spent observing ward activity).

##### Documentary analysis

All participants who consent to the quantitative arm of the feasibility trial will be asked at the 30-day post-discharge follow-up if they received a YCNY booklet in hospital and, if so, whether they would be willing to return it to the research team. Any returned booklets will be analysed to explore how they have been used.

#### Qualitative data analysis

Qualitative data will be analysed using a ‘pen portrait’ method [31]. Pen portraits are typically used to synthesise data across sources. Data related to each ward will be drawn together to describe how the intervention was implemented, how staff and patients engaged with the intervention, and what the experience was for patients following discharge. Pen portraits will subsequently form the unit of analysis and be subjected to a thematic analysis [32], before being synthesised, with coding specifically pertaining to issues of acceptability and feasibility.

### Sub-study to assess discharge destinations

The target patient population for this programme of work is older people who transition from hospital back into their own home (rather than 24-h care, e.g. a nursing or care home). To test the effectiveness of the intervention in the definitive cRCT, primary outcome data (30-day emergency readmissions) are required from 7000 patients which we had planned to gather at a ward level via routinely collected administrative data. However, our previous work has highlighted that patients are coded as being discharged to their ‘usual place of residence’ which does not distinguish those who go from and to their own homes (our target population) and those who go from and to 24-h care/nursing homes. Not understanding the size of this coding problem represents a major threat to the internal validity of the definitive trial. As such, a separate sub-study will explore the actual discharge destinations of patients on participating wards who are aged 75 years or over and are coded as being discharged to their ‘usual place of residence’.

Confidentiality Advisory Group permissions have been gained to access patient medical records without consent. Trusts will identify a consecutive sample of 10 patients from each participating ward who are aged 75 years and over and have been coded as discharged to their ‘usual place of residence’. Their medical records will be accessed to identify their actual discharge address and this will be categorised as being either: their own or a relative’s home; a nursing or care home; intermediate care; or other. The research team will receive anonymised, aggregated ward-level data detailing the total number of patients discharged to each category.

